### Sample size

To calculate the sample size, effect sizes found in previous studies on the topic have been considered. Grenyer et al. [30] tested a group psychoeducation protocol for caregivers of people with BPD in a controlled study that reports medium to large effect sizes (dyadic adjustment, *d* = 0.78; family empowerment, *d* = 1.4). Moreover, Grenyer obtained significant improvements on measures of illness burden between post-assessment and 12-month follow-up, with medium effects (*d* = 0.45). These effects are in line with the literature on psychological treatments for relatives of people with ED (Positive Caregiver Experience, *g* = -0.80) [14]. Given these data, an effect size of 0.50 is expected in the present study, adopting a conservative approach. Because our design includes two experimental conditions, t-tests are assumed for the statistical analyses. Considering an alpha of 0.05 and a statistical power of 0.80 in a two-tailed t-test, the total sample size needed to reach an effect size of 0.60 in loading is 90 participants (45 participants per experimental condition). To control for the maximum possible loss of subjects during treatment, based on the literature on previous programs for family members of BPD or ED patients, a dropout rate of 30% is expected [34–36]. Therefore, the required sample size should contain 124 participants in all (62 participants per group), as Fig. 1 shows. These calculations were carried out using the software program G*Power 3.1 [44].

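### The plan expects an effect of 0.50 but sizes the trial at 0.60, so power at its own expected effect is about 65% (63% after the planned loss), not 80%

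*Protocol article*

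**What the plan says.** Everything on this point stands in one paragraph, the Sample size section under Methods in the protocol article.

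- After citing earlier effects in relatives of patients, including d = 0.45 for illness burden, it fixes the planning value: "an effect size of 0.50 is expected in the present study, adopting a conservative approach".
- It names the test: "t-tests are assumed for the statistical analyses".
- It then gives the operating characteristics, "Considering an alpha of 0.05 and a statistical power of 0.80 in a two-tailed t-test", and the result: "the total sample size needed to reach an effect size of 0.60 in loading is 90 participants (45 participants per experimental condition". The word loading appears to mean burden, one of the family members' primary outcomes.
- It allows for loss, "a dropout rate of 30% is expected", and sets enrolment: "the required sample size should contain 124 participants in all (62 participants per group".
- It names the tool: "These calculations were carried out using the software program G*Power 3.1".

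No sentence explains the move from 0.50 to 0.60.

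**The concern.** The paragraph argues for one effect size and computes with another. The change goes in the less cautious direction, because a larger assumed effect needs fewer participants. A reader who follows the argument will take 90 analysed participants to give 80% power for the expected 0.50.

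This is a separate matter from where 0.50 comes from and whether it is cautious. Even if 0.50 is accepted in full, the sample size was not computed for it.

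The trial is described as a superiority trial, and this paragraph is the only justification of its size in the article. If the true effect is 0.50, the risk of a non-significant result is well above the 20% that the stated power implies. Such a result could then be read as evidence that the programme does not help.

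**Working it through.** **Inputs, all from the Sample size section:** expected effect 0.50; effect used in the calculation 0.60; two-sided alpha 0.05; power 0.80; independent two-sample t-test; equal arms; 30% loss; 62 enrolled per arm.

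**Formula.** With n per arm and standardised difference d, the t statistic has 2n − 2 degrees of freedom and noncentrality λ = d × √(n/2). Power is the probability that |t| exceeds the two-sided 5% critical value. This is the noncentral-t calculation that the named software uses.

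**1. The plan's own figure, d = 0.60.** Solving for 80% power gives n = 44.6, so 45 per arm and 90 in total. Check: λ = 0.60 × √22.5 = 2.846, critical value 1.987 on 88 degrees of freedom, power 80.4%. The stated 90 is reproduced exactly.

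**2. The same calculation at the expected effect, d = 0.50.** Solving gives n = 63.8, so 64 per arm and 128 analysed. Allowing for 30% loss, 64 / 0.70 = 91.4, so 92 per arm and 184 enrolled.

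**3. Does another variant give 90 at 0.50?** A one-sided test at 0.05 needs 51 per arm, 102 in total. The normal approximation for the two-sided test needs 63 per arm. Neither gives 45.

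**4. Power at d = 0.50 with the planned numbers.** Loss of 30% leaves 62 × 0.70 = 43.4, taken as 43 per arm.

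| Analysed per arm | λ | Power at 0.50 | Chance of missing it |
|---|---|---|---|
| 45 (as computed in the plan) | 0.50 × √22.5 = 2.372 | 65.0% | 35% |
| 43 (62 less 30%) | 0.50 × √21.5 = 2.318 | 63.0% | 37% |
| 62 (nobody lost) | 0.50 × √31 = 2.784 | 78.9% | 21% |

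**5. Effect detectable with 80% power.** This is 0.597 with 45 per arm and 0.611 with 43 per arm.

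**6. For context.** At d = 0.45, the only illness-burden effect the paragraph cites, power is 56% with 45 per arm and 54% with 43.

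**The case against.** **The plan attaches 80% to 0.60, and that calculation is right.** This is true. The paragraph never says in so many words that power is 80% at 0.50. The defect is an unexplained change of input within the paragraph, not a mistake inside the calculation. But 0.60 is not the effect the plan says it expects, and no other reason for it, such as a smallest important difference, is given.

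**One value may be a typing slip.** This is possible. As 45 per arm fits 0.60, that value was evidently the one entered in the software. If 0.50 is the slip, 90 and 80% agree with each other, but the text can no longer present 0.50 as its cautious basis. If 0.60 is the slip, 90 is too few. The text must change either way.

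**The two values could describe different quantities,** 0.50 for the study in general and 0.60 for burden. The paragraph does not say so, and its one cited burden effect, 0.45, is lower than both.

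**The real analysis may have more power than a t-test.** The Data analyses section plans repeated-measures ANOVA and mixed-effects models, and people who stop treatment may still give outcome data. Baseline adjustment divides d by √(1 − r²), where r is the correlation between baseline and outcome. The article gives no r, so the following are assumptions only. With 43 to 45 per arm, power at 0.50 would be about 67% to 69% for r = 0.3, 75% to 77% for r = 0.5, and 82% to 83% for r = 0.6. This stands as a caveat. It cannot be credited to the plan, which bases its calculation on t-tests.

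**The 124 enrolled give about 79% at 0.50.** They do so only if nobody is lost. The extra participants were added to cover the 30% loss and cannot also be counted as analysed.

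**The 63% contains a second, smaller problem.** Keeping 90 after 30% loss needs 90 / 0.70 = 128.6, so 129 (130 with equal arms), where the plan has 124. The figure that isolates the change of effect size is 65%.

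**Conclusion.** The concern holds. The paragraph expects 0.50 and computes its sample size at 0.60. On its own terms (unadjusted two-sided t-test, alpha 0.05, equal arms), power at 0.50 is 65% with the 45 per arm it derives and 63% once 62 per arm are reduced by 30%. The consistent number for 0.50 is 128 analysed, 38 more than the 90 stated.

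These figures rest on 0.50 being the intended design value and on those who drop out giving no outcome data. Full retention, or a strong correlation between baseline and outcome with an adjusted analysis, would bring power near 80%. The article expects the opposite of the first and gives no figure for the second. The text has to be corrected whichever value was intended, because the trial's size rests on it.

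**What to change.** State which effect size is the design assumption and use it throughout the Sample size section.

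If enrolment stays at 124, replace the present statement with wording to this effect: with 124 randomised and about 43 to 45 analysed per arm, a two-sided t-test at alpha 0.05 has 80% power for a standardised difference in burden of about 0.60, and about 63% to 65% power for a difference of 0.50; a non-significant result does not exclude 0.50. Remove the wording that presents the calculation as resting on 0.50. This costs a few sentences and a less favourable power statement, with no extra participants. As the article reports that recruitment is under way, the change should be made before results are interpreted.

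If 80% power at 0.50 is really required under the stated test and loss, the matching numbers are 128 analysed and 184 randomised, which is 60 more than the 124 planned. If the sponsor prefers to rely on a gain from the planned mixed model, it should state the assumed correlation and recompute the power on that basis.

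### The enrolment target of 124 does not follow from 90 evaluable participants and 30% dropout; that calculation gives 130, and 124 leaves about 43 per arm where 45 are needed

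*Protocol article*

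**What the plan says.** The Sample size section of the protocol article sets out a short chain.

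- Test and error rates: "Considering an alpha of 0.05 and a statistical power of 0.80 in a two-tailed t-test".
- Evaluable number: "the total sample size needed to reach an effect size of 0.60 in loading is 90 participants (45 participants per experimental condition").
- Attrition: "a dropout rate of 30% is expected". Its purpose is given as "To control for the maximum possible loss of subjects during treatment".
- Conclusion, introduced as following from the above: "the required sample size should contain 124 participants in all (62 participants per group").

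The section gives no other dropout rate and no other inflation rule. It also states that "an effect size of 0.50 is expected in the present study, adopting a conservative approach", which is not the effect size used to reach 90.

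**The concern.** The purpose of inflating a sample size is that, once the expected losses have occurred, the required number remains. Here the enrolment target is presented as the result of 90 and 30%, but applying 30% loss to 124 leaves fewer than 90.

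Two things depend on this. First, the paragraph promises 80% power at d = 0.60 under its own attrition assumption, and the target does not quite deliver it. Second, 124 is the figure the trial recruits to, so a borderline or null result will be read against a stated power that the arithmetic does not support.

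A secondary point concerns timing. The 30% is described as loss during treatment, which for the FC arm lasts three months (Interventions section). The Data analyses section also plans an analysis at 12-month follow-up, and any loss after treatment is outside the allowance.

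**Working it through.** **Inputs (all from the Sample size section).** Two-sided alpha 0.05; power 0.80; independent-samples t-test; equal arms; d = 0.60; 45 evaluable per arm; dropout 30%; stated target 62 per arm.

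**Step 1: reproduce the evaluable number.** The exact (noncentral t) calculation for d = 0.60 gives n = 44.6 per arm, rounded up to 45, or 90 in all. Power with 45 per arm is 80.4%. The stated 90 is correct.

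**Step 2: inflate for dropout.** The formula is n randomised = n evaluable / (1 − dropout).

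- Per arm: 45 / 0.70 = 64.3, rounded up to 65, so 130 in all.
- On the total: 90 / 0.70 = 128.6, rounded up to 129, which becomes 130 with equal arms.
- The common shortcut n × (1 + dropout): 90 × 1.3 = 117.

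None of these gives 124. The shortfall against 130 is 6 participants, 3 per arm.

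**Step 3: work backwards from 124.**

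- 62 × 0.70 = 43.4 per arm; 124 × 0.70 = 86.8 in all. Both are below the required 45 and 90.
- Dropout at which 62 per arm still leaves 45: 1 − 45/62 = 0.274, or 27.4%.

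**Step 4: consequence for power (two-sided t-test, alpha 0.05).**

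| Evaluable per arm | Power at d = 0.60 | Power at d = 0.50 | Detectable d at 80% power |
|---|---|---|---|
| 45 (as required) | 80.4% | 65.0% | 0.597 |
| 43.4 (62 × 0.70, unrounded) | 78.9% | 63.4% | 0.608 |
| 43 (rounded down) | 78.5% | 63.0% | 0.611 |

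The slip costs 1.5 to 1.9 percentage points of power at d = 0.60. The d = 0.50 column is shown because the section calls that effect the expected one. Power there is already only 65.0% with the full 45 per arm, so almost all of that shortfall comes from sizing on 0.60, not from the inflation step.

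**Step 5: could a different starting number explain 124?** The normal approximation gives 44 per arm (88 in all), and 88 / 0.70 = 125.7, so 126. That is closer but still not 124, and it contradicts both the stated 90 and the stated t-test.

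**Step 6: later loss (illustration only).** The document gives no rate of loss after treatment. If total loss by 12 months were 35% or 40% (assumed), 62 × 0.65 = 40.3 or 62 × 0.60 = 37.2 would remain per arm. With 40 or 37 per arm, power at d = 0.60 is about 75% or 72%.

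**The case against.** The strongest reply is that the gap is too small to matter. Six participants and under two points of power change no design decision, and the section describes 30% as a ceiling as well as an expectation, so on that reading the 45 is missed only if dropout falls between 27.4% and 30%. This is fair as to size and keeps the point modest. It does not make 124 the result of 90 and 30%.

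A second reply is that 43 per arm counts completers only. The Data analyses section plans intention-to-treat analysis by mixed-effects models with maximum likelihood, which keeps people who drop out after baseline. Depending on the correlation between baseline and outcome, which the document does not give, such an analysis could make up two participants per arm. With 43 per arm, a baseline-adjusted analysis does so if 43/(1 − r²) is at least 45, that is r of about 0.2 or more. A change-score analysis needs 43/[2(1 − r)] to be at least 45, that is r above about 0.52. This limits the practical loss. But the Sample size section does not argue this way: it sizes on a t-test and inflates so that losses do not eat into the 90.

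Third, sizing for post-treatment is a legitimate choice, and later loss is a question of scope, not of arithmetic. That is accepted, and the 12-month remark is secondary for that reason.

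Finally, the mismatch between the expected 0.50 and the 0.60 used is a larger and separate problem. Correcting 124 alone would not resolve it, and reconciling the effect size could change 90 and 124 together.

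**Conclusion.** The stated figure is wrong. From 45 evaluable per arm and 30% dropout the target is 65 per arm, 130 in all. The stated 62 per arm leaves about 43 at that dropout rate, with 78.5% to 78.9% power at d = 0.60 and a detectable effect of about 0.61. It meets the plan's own requirement only if dropout does not exceed 27.4%.

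This rests on the section's own inputs (two-sided t-test, equal arms, 30% loss in each arm) and on completers as the evaluable set, which is how the section counts them. The effect on power is small and validity is untouched, but the enrolment figure should be described correctly.

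**What to change.** Recruitment is under way according to the Data Availability statement, so the simplest course is to keep 124 and correct what is said about it. Either of these is accurate:

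- 124 participants (62 per arm) allow for up to 27% dropout while retaining 45 per arm; or
- with 30% dropout, 124 participants leave about 86 evaluable (43 per arm), giving about 78% power for d = 0.60 and 80% power for d = 0.61.

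Add that the allowance covers loss up to post-treatment only, or give the power at 12 months separately with the loss assumed for it. If the effect-size assumption is reconciled at the same time, rewrite both statements together, since the 45, the 27% and the 78% all depend on d = 0.60.

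The cost is one corrected sentence and a slightly lower stated power. No extra participants and no design change are needed.

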**Fig. 1 Fig1:**
[figure not shown]
Flow Chart

### Procedure

Family members of patients with ED-PD will be given the opportunity to participate in the study. Once they have signed the informed consent, an expert clinician will perform the assessment of each participant to check that the inclusion and exclusion criteria are met, and an independent investigator, unaware of the characteristics of the study, will be contacted to perform the randomization. At all times, for randomization purposes, an experimenter from outside the research team will assign each family member to one of the two study conditions (FC: ED-PD or TAU-O) using a random number software program. The randomization sequence will be concealed from the clinicians participating in the study. Independent assessors will administer the assessment protocol to the participants without being aware of the experimental condition to which they belong (FC: ED-PD or TAU-O). Patients will also be assessed before starting the intervention programs for relatives. After the assessment has been completed, all the relatives will start to receive the intervention in the condition to which they have been assigned, and the patients will participate in their current treatment or care. At the end of the intervention, the assessment protocol will be re-administered to both relatives and patients, again by independent assessors, and the same thing will be done at the 12-month follow-up.

### Ethics

All methods will be conducted in accordance with the ethical standards of the declaration of Helsinki accordance with relevant guidelines and regulations. Researchers adhere to the Helsinki Convention and the World Psychiatric Association's Madrid Declaration on clinical research. All participants will be volunteers who have given their informed consent to participate in the study. All eligible participants will be given oral and written information about the study and the two intervention modalities. Specifically, they will be informed that they may leave the study at any time without giving an explanation, and that this decision will in no way affect their family member's regular treatment at the center. The selection and evaluation of the participants will be performed by qualified personnel who will not know to which condition a given participant has been assigned, and the treatments will be carried out by qualified and expert professionals. The Ethics Committee of the University of Valencia (Valencia, Spain) approved this study with number UV-INV_ETICA-1955599. The trial was registered at clinicalstrial.gov as NCT05404035, June 3rd 2022.

### Interventions

#### Family connections for relatives of people with eating disorders and personality disorders (FC: ED-PD)

The intervention lasts three months and includes 12 sessions with a weekly two-hour group format. The FC program [34]) is divided into six modules, but the research team developed the program adapted to ED and PD in seven modules, which are described below [34]:Module 1Presentation of the program, objectives, structure, tasks, etc. Up-to-date information and research on ED and PD (Epidemiology, frequency, Risk factors, and protective factors).Module 2 Psychoeducation on the development of ED and PD, explanatory theories, available treatments, and comorbidity with PD.Module 3 Emotional regulation skills, skills of acceptance, validation, approach, and awareness, and to decrease emotional reactivity.Module 4 Skills to improve the quality of relationships in family interactions (letting go of guilt and anger, acceptance skills in relationships).Module 5Communication skills and effective self-expression.Module 6 Problem management and making safe plans for crisis management.

All the modules include practice exercises, video viewing, and homework assignments. In addition, throughout the program, with the goal of increasing social support, the FC program provides a forum where participants can stay in touch and share common problems and solutions.

#### Optimized treatment as usual (TAU-O)

Family members in this condition will continue to receive the usual treatment provided by their referral care center. In addition, we will optimize the treatment they are currently following, based on the recommendations of the international guidelines for the treatment of ED [45]. There will be one three-hour session in group format, with the following components:Module 1 Up-to-date information and research on ED and PD (epidemiology, frequency, risk factors, protective factors). Psychoeducation on the development of ED and PD. Explanatory theories. Available treatments and comorbidity.

In both conditions, after each face-to-face session, the participant will be asked to review the contents addressed during the session as homework (independently of the homework corresponding to the specific module being addressed). All the interventions with family members will be performed by clinical psychologists or general health psychologists with at least a master's degree or a doctoral degree, and with previous training in administering the programs.

#### Treatment of patients

With regard to the patients’ treatment, the routine treatment they receive in their centers of reference will be followed. All the interventions will be carried out by the clinical psychologists and psychiatrists working in these centers.

## Measures

### Family members’ measures (participants)

#### Primary outcomes

*Record of critical family-patient incidents* number of Binge eating and vomiting (purging) episodes in the past three months, number of serious arguments between patient and caregivers in the past three months, number of days of self-injury in the past three months, number of episodes of verbal/physical violence with caregivers in the past three months, number of visits to the psychiatric emergency department in the past three months, number of unscheduled therapy sessions in the past three months (face-to-face, phone calls, etc.).

*Burden assessment scale* [46]: It is a 19-item scale that assesses caregivers’ objective and subjective burden due to their loved one’s illness within the past six months. Items are rated on a 4-point Likert scale ranging from 1 (nothing) to 4 (a lot). Higher total scores indicate stronger burden. The scale shows adequate validity and reliability (Cronbach’ alpha ranges from 0.89 to 0.91) [47]

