### Study design

First, a pilot feasibility study will be carried out using focus groups to explore the opinions of relatives of ED-PD patients. Semi-structured interviews will be used. The research design will follow the criteria established by Cooke et al. [40], and for the development of the focus groups, the guide developed by Breen [41] for this type of methodology will be used. Second, a randomized controlled clinical trial will be conducted following the CONSORT (Consolidated Standards of Reporting Trials) guidelines http://www.consort-statement.org/ [42, 43]. This study is a superiority trial. The study design consists of a two-arm randomized controlled trial (RCT). On the one hand, there will be two conditions: Family Connections (FC-ED—PD) or Treatment as usual optimized (TAU-O), and family members will be randomized to one of the two groups. -A between-subjects design will be used with three assessment points: pre-treatment, post-treatment, and a follow-up 6 and 12 months after the end of treatment. Once the study has been explained and the informed consent has been signed, participants will be randomly assigned to one of two experimental conditions: 1) The adaptation of the FC protocol for relatives of ED-PD patients (FC: ED-PD) will be applied; 2) The Treatment as Usual Optimized Treatment (TAU-O) protocol will be applied. Randomization will be performed by an external researcher who will not participate in any of the phases of the project. The randomization sequence will be hidden from the evaluators participating in the study. The G*Power 3.1 software [44] will be used for this purpose. Assessment of participants will be carried out by a clinician other than the professional administering the treatments. Upon completion of the randomized controlled clinical trial, in-depth interviews will be conducted with family members who have successfully completed the intervention (e.g. clinically significant change) and with family members who drop out of the intervention. In all the potential groups, the aim will be to explore participants' experiences in order to learn about barriers and facilitators of the intervention.

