### Measures‑patients

#### Primary outcomes

*The eating attitudes test‐26* [60]. in its Spanish version [61]. *This scale is used to evaluate the patients*. It is a 26-item self-report that assesses attitudes toward eating. Items are rated on a 6-point Likert scale ranging from 1 (never) to 6 (always). The reliability analysis indicated good internal consistency [60, 62–65].

*Patient health questionnaire* [66]. in its Spanish version [67]. *This scale is used to evaluate the patients*. It assesses each of the nine DSM-IV criteria for depression through nine items. Items are rated on a 4-point Likert scale ranging from 0 (not at all) to 3 (nearly every day).

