### Data analyses

Regarding data analysis, the results of the pilot feasibility study using focus groups will be analyzed using thematic analysis in order to identify the topics that emerge from the focus groups [72]. Data reporting will be carried out following the COREQ guidelines [73]. In addition, qualitative research quality criteria recently developed by Levitt et al. [74] will be pursued in order to achieve what the authors refer to as methodological integrity in the qualitative field.

In the controlled clinical trial, the CONSORT guidelines [43] will be followed. First, participants' scores in the two conditions will be compared before the intervention to check that there are no significant differences between them on the outcome measures and that they are, therefore, comparable after randomization. ANOVAs will be conducted for continuous variables and Chi-square tests for categorical variables. For outcome measures at post-treatment, we will study whether the assumption of homoscedasticity is met with Levene's test. If this assumption is met, repeated-measures ANOVAs and F-tests will be used to compare the two experimental conditions. If the homoscedasticity assumption is not met, the Brown-Forsythe test will be applied. F-tests for statistical significance will be followed by post hoc comparisons. In particular, Tukey will be used when the homoscedasticity assumption is met, and Games-Howell if the homoscedasticity assumption is not met. Appropriate analyses will also be carried out to calculate intervention effect sizes and confidence intervals. The intention-to-treat principle will be used when analyzing pre- and post-treatment data and at 12-month follow-up, using mixed-effects models with full information and maximum likelihood estimation. To complement the results of ANOVAs and post hoc comparisons, effect sizes will be calculated using the standardized mean difference proposed by Cohen [75]. These effect sizes will be calculated to assess changes within and between groups, all based on a pooled standard deviation.

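### Four instruments in two populations (up to nine variables) are called primary without ranking, primary time point or success rule, while the sample size covers one test of burden

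*Protocol article*

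**What the plan says.** **Relatives.** The Primary outcomes part of the family members' measures names a record of critical incidents and the Burden Assessment Scale. The record holds six counts, each over three months: binge/purge episodes, then "number of serious arguments between patient and caregivers in the past three months, number of days of self-injury in the past three months", then violence episodes, psychiatric emergency visits and unscheduled therapy sessions. No total or composite score is defined.

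**Patients.** A second Primary outcomes part, under the patients' measures, names EAT-26 and the Patient Health Questionnaire, of which it says "It assesses each of the nine DSM-IV criteria for depression through nine items".

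**Sample size.** The calculation is for one comparison, a two-sided t-test at 0.05 with 80% power. The result is given as "the total sample size needed to reach an effect size of 0.60 in loading is 90 participants (45 participants per experimental condition". I read *loading* as burden.

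**Decision rule.** Study design calls this a superiority trial. Objectives and hypotheses judges effectiveness by changes on the evaluation instruments in general, after treatment and at 12 months, with eight expectations listed side by side.

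**Analysis.** Data analyses plans repeated-measures ANOVA and mixed-effects models, with Tukey or Games-Howell post hoc tests. It states "The intention-to-treat principle will be used when analyzing pre- and post-treatment data and at 12-month follow-up".

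**Visits.** Study design announces "three assessment points: pre-treatment, post-treatment, and a follow-up 6 and 12 months after the end of treatment".

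**The concern.** A superiority trial needs one confirmatory question, or a stated way of sharing the error rate among several. Here four instruments carry the same primary label in two populations, but the alpha and power calculation belongs to one of them. Nothing says which result decides whether the programme beats optimized usual treatment, or when it is measured.

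The post hoc tests do not fill this gap. Tukey and Games-Howell work within one outcome, and with two arms there is only one between-group comparison to protect.

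The false-positive rate behind the superiority claim is therefore not held at 5%. If alpha were later divided among all the primaries, the planned number would no longer give 80% power. The patient outcomes add a further gap: relatives are randomized and counted in the sample size, and no number of patients is given.

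**Working it through.** **Inputs.** Two-sided alpha 0.05, power 0.80, effect size 0.60 and 45 per arm come from Sample size. The outcome counts come from the two Primary outcomes parts:
- Instruments: 2 (relatives) + 2 (patients) = 4.
- Variables with the six counts tested separately: 6 + 1 + 1 + 1 = 9.
- Relatives only: 2 instruments, or 6 + 1 = 7 variables.

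**Step 1: reproduce the plan's figure.** The normal approximation is n per arm = 2(1.960 + 0.842)² / 0.60² = 43.6, so 44. The exact t-test (noncentral t, as in G*Power) gives 44.6, so 45 per arm and 90 in total, as stated. The number is right for one test at the full 0.05. Nothing is reserved for other outcomes.

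**Step 2: chance of at least one false positive**, k tests at 0.05, one time point, independent: 1 − 0.95^k. The right-hand column is a simulation (200,000 multivariate-normal draws) with an assumed equal correlation between outcomes.

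| Reading | k | Independent | Correlation 0.7 to 0.3 |
|---|---|---|---|
| Relatives, instruments | 2 | 1 − 0.9025 = 9.75% | not run |
| All, instruments | 4 | 1 − 0.8145 = 18.5% | 13.2% to 17.4% |
| Relatives, variables | 7 | 1 − 0.6983 = 30.2% | 17.8% to 27.2% |
| All, variables | 9 | 1 − 0.6302 = 37.0% | 20.2% to 32.4% |

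**Step 3: cost of keeping every primary**, Bonferroni at effect size 0.60 and 80% power:
- Four tests: alpha 0.05/4 = 0.0125 needs 64 per arm. Power at 45 per arm is 62%.
- Nine tests: alpha 0.05/9 = 0.00556 needs 75 per arm, 150 evaluable, and 150/0.7 = 215 with 30% dropout. Power at 45 per arm is 50%.

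**Step 4: recall period against time point.** The burden scale looks back six months and the programme lasts three. A score taken as the programme ends therefore covers about 6 − 3 = 3 months before it began. A score 12 months after the end covers months 6 to 12 after treatment and no pre-treatment time.

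**Step 5: visit schedule.** Study design counts three assessment points but lists four: before, after, 6 months and 12 months. The Abstract, Objectives and hypotheses, Procedure and Data analyses mention only the one-year or 12-month follow-up.

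**The case against.** **The level of each test is not stated.** Alpha 0.05 appears only in Sample size, and the allocation of alpha may sit in an analysis plan that is not shown. This stands as a limit: testing every primary at 0.05 is an inference. It does not remove the point, because the primary labels and the one-test sizing are fixed in this article. A later adjustment without re-sizing would also lower power as in Step 3.

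**No rule says that any one significant outcome is enough.** Correct. A reader might infer that one positive result out of nine would be declared success. The article states neither that rule nor an all-must-succeed rule. The fault is that the rule is left open.

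**Nine is the highest count.** Also correct. The incident record is one named instrument, so four is a fair lower reading for both populations. The patients' outcomes may serve mainly the objective on association with relatives' change, which is why the relatives-only figures are shown too. Nothing in the article, however, excludes EAT-26 and PHQ from the efficacy comparison.

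**Repeated visits.** A reader might multiply further: 9 × 2 = 18 tests give 60% and 9 × 3 = 27 give 75% under independence. The article does not support these figures. Repeated-measures and mixed models need not produce a separate test per visit, repeated scores of one variable are not independent, and Data analyses plans no 6-month analysis.

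**Conclusion.** The point holds. Several unranked primary outcomes in two populations, no primary time point and no success rule stand beside a sample size built for one burden test. Under a 0.05 test of each primary at one time point, the false-positive risk is 18.5% to 37% under independence, and about 20% to 32% for nine variables at assumed correlations of 0.7 to 0.3. For relatives' outcomes alone it is 9.75% to 30.2% under independence. The 0.05 level per test, the correlations and the reading of *loading* as burden are assumptions.

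The visit-schedule conflict is real but separate and smaller. So are two other inconsistencies in Sample size, which this point does not rely on. The text announces "an effect size of 0.50 is expected in the present study, adopting a conservative approach" but computes with 0.60. It also states "a dropout rate of 30% is expected" but gives 124 in total, where 90/0.7 is 129.

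**What to change.** 1. Name the Burden Assessment Scale total score in relatives as the single primary outcome, compared between arms at one stated time point. The 12-month follow-up is cleaner than the post-treatment visit because of the six-month recall.
2. Make the six incident counts, EAT-26 and PHQ secondary. If a confirmatory claim on any of them is wanted, list those outcomes in advance and test them by Holm at 0.05 only if the primary is significant, so that the overall error stays at 5%.
3. In Sample size, write Burden Assessment Scale in place of *loading* and name the time point.
4. Separately, state one visit schedule in every section: either carry the 6-month visit into the Abstract, Objectives and hypotheses, Procedure and Data analyses, or remove it from Study design.

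**Cost.** Multiplicity then requires no extra participants, since 45 evaluable per arm keep 80% power at effect size 0.60 for the one test. Fewer outcomes can be called primary. The trial is registered, ethics-approved and recruiting, so this is a substantive change that needs a dated protocol and registry entry before analysis. The 30% dropout allowance is described as loss during treatment, so the team should check that it also covers loss to 12 months.
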